**PROTOCOL SYNOPSIS**

| **Title** | **Safety and Feasibility of Allogeneic Cord Blood-Derived Cell Therapy in Preterm Infants with Severe Brain Injury** |
| --- | --- |
| **Objectives** | Primary   1. To evaluate feasibility of availability of allogeneic umbilical cord blood cells (UCBCs) in surviving preterm infants with severe brain injury. 2. To evaluate safety of administration of allogeneic UCBCs in surviving preterm infants with severe brain injury.   Secondary   - 1. To evaluate the effect of administration of allogeneic UCBCs on short and long-term clinical outcomes.   2. To evaluate the effect of administration of allogeneic UCBCs on immune responses, as measured by cytokine levels. |
| **Outcomes and outcome measures** | Primary outcomes   - 1. Feasibility: Availability of at least 4/6 HLA-matched allogeneic UCBCs sourced from the BMDI Cord Blood Bank for >60% of eligible infants.   2. Safety: Absence of serious adverse events related to UCBCs administration during and for 48 hrs post-infusion and the absence of graft versus host disease (GVHD) in the first three months after cell infusion.   Secondary outcomes   - 1. Clinical outcomes      1. Death, until 24 months of corrected age      2. Moderate to severe bronchopulmonary dysplasia, assessed at 36 weeks of postmenstrual age      3. Severe retinopathy of prematurity, assessed before discharge      4. Necrotising enterocolitis, assessed before discharge      5. Culture proven sepsis, assessed before discharge      6. Developmental delay, assessed anytime until 24 months of corrected age      7. Cerebral palsy, assessed anytime until 24 months of corrected age      8. Blindness, assessed any time until 24 months corrected age      9. Deafness, assessed any time until 24 months corrected age   2. Laboratory outcomes: Effect of allogeneic UCBCs on infant’s cytokines levels, including interleukin 1b (IL-1b), IL-6, Tumour Necrosis Factor (TNF-α), and IL-10 just before UCBC administration and 1-day and 7-day post administration |
| **Trial population** | 20 preterm infants with severe brain injury, with 10 each in each stratum (<28 weeks, ALLO-1 trial and 28-37 weeks, ALLO-2 trial), will be enrolled to receive UCBCs, if appropriate matching is achieved |
| **Description of sites enrolling participants** | This trial will only recruit participants from Monash Children’s Hospital |

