           6. Developmental delay, assessed based on early **(**General Movements, Hammersmith Neonatal/Infant Neurological Examination at 3-4 months corrected age) or late (Bayley Scales of Infant Development, (BSID) IV at 18-24 months corrected age) neurodevelopmental assessments
           7. Cerebral palsy, assessed based on early **(**General Movements, Hammersmith Neonatal/Infant Neurological Examination at 3-4 months corrected age) or late (BSID-IV and Gross Motor Function Classification System Expanded and Revised at 18-24 months corrected age) neurodevelopmental assessments
           8. Blindness, assessed any time before 18-24 months corrected age
           9. Deafness, assessed any time before 18-24 months corrected age
        2. Laboratory outcomes: A broad array of cytokines will be assessed on the infant’s serum, including interleukin 1b (IL-1b), IL-6, Tumour Necrosis Factor (TNF-α), and IL-10 just before UCBC administration and 1-day and 7-day post administration.
  2. ***UCBCs administration***

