At three months corrected age: General movements assessment and Hammersmith infant neurological examination

At 12 months of corrected age: Gross Motor Function Measure-66 and Infant–toddler Social and Emotional Assessment

At two years of corrected age: Bayley Scales of Infant and Toddler development-IV, and medical assessment for disability

- - - 1. Relevant laboratory tests will be performed to monitor the response and to detect any adverse events, such as GVHD

Before the infusion: Cytokine analysis, including interleukin 1b (IL-1b), IL-6, Tumour Necrosis Factor (TNF-α) and IL-10

24 h after the infusion: Cytokine analysis, full blood examination (FBE), chimerism assessment and LFTs

4 day, 1 week and 1 month chimerism assessment

1 week, 1 month and 3 months post-transfusion: FBE and LFTs

Chimerism assessment will be repeated at 3 months if there are detectable donor cells at 1 month testing (optional assessment)

Lymphocyte subset analysis will also be performed if white cell count is low, which is consistent with GVHD

- - 1. **Data Safety Monitoring Board (DSMB)**: A DSMB consisting of a neonatologist, and paediatric neurologist or cell therapist or haemato-oncologist will be established to review all the adverse events. All serious events will be reported to DSMB within 7 days of occurrence.
       - 1. *Interim analysis:* DSMB will be requested to conduct an interim analysis following the enrolment of five patients in each group to assess the feasibility and adverse events. DSMB and HREC will also review whenever there is a serious event to ensure it is safe to continue the trial.
         2. *Criteria for premature termination of trial*: DSMB and HREC will be consulted for an independent review of trial conduct, progress and any serious events related to cell therapy, which will further determine whether the trial requires premature termination. No predetermined interim analysis will be conducted. The analysis will only be conducted after at least 10 infants have been recruited in each stratum.
    2. Reporting:
       1. Any events occurring after the allogeneic UCBC therapy will be reported to the relevant parties. Events will be categorised as per the National Health and Medical Research Council 2016 recommendation^31^ and report any related or unrelated events

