**INTERVENTION (Examine**, **blood** for cytokines, **administer UCBCs)**

**Blood** for cytokines (24 h) & assess for side effects (up to 48 h)

**Blood** for chimerism (4d)

**Blood** for FBE, LFTs and chimerism (1w, 1m)

**GVHD assessment** at 2 m

**Blood** (FBE/LFTs), & **GVHD assessment** (3m)(***SAFETY***)

**MRI** at TEA

**Assessments: Neurological** (3, 12, 24 m) and **GVHD** (6, 9, 12, 18, 24m)

**Table 1**: Safety, adverse events, and neurological outcome monitoring

| Timeline | Cardiorespiratory monitoring | Infection monitoring | Physical examination | Cytokine analysis | FBE*, chimerism assessment and LFT | Neurodevelopmental assessment | Neuroimaging |
| --- | --- | --- | --- | --- | --- | --- | --- |
| -2 to 0 h | √ | √ | √ | √ |  |  |  |
| 0 to 48 h | √ | √ |  |  |  |  |  |
| 24 h |  |  | √ | √ | √ |  |  |
| 4 d |  |  |  |  | √ (Chimerism only) |  |  |
| 7 d |  |  | √ |  | √ |  |  |
| 1 m |  |  | √ |  | √ |  |  |
| 2 m |  |  | √ |  |  |  |  |
| 3 m |  |  | √ |  | √ (Chimersim is optional) | √ (TEA) | √ (MRI at TEA) |
| 6 m |  |  | √ |  |  | √ (3 m CA) |  |
| 9 m |  |  | √ |  |  |  |  |
| 12 m |  |  | √ |  |  | √ (12 m CA) |  |
| 18 m |  |  | √ |  |  |  |  |
| 24 m |  |  | √ |  |  | √ (24 m CA) |  |

**Note**: CA, corrected age; FBE, full blood examination (*-lymphocyte subset analysis for patients with abnormal FBE consistent with GVHD, and chimerism analysis will be repeated at 3, 6 or 12 months if there are detectable donor cells at 1 and/or 3 months testing); LFT, liver function test; MRI, magnetic resonance imaging; TEA, term equivalent age

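### The day-7 cytokine sample in the secondary laboratory outcome is missing from the laboratory list, Figure 1 and Table 1

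*Combined protocol and SAP*

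**What the plan says.** **Outcome definition.** The laboratory outcome under Methods, Outcomes, sets cytokine measurement "just before UCBC administration and 1-day and 7-day post administration". The Protocol Synopsis gives the same three times: "IL-10 just before UCBC administration and 1-day and 7-day post administration". Cytokine levels are the stated measure of the secondary objective on immune response.

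**Laboratory list (Safety monitoring and reporting, Monitoring).** Cytokines appear twice. The pre-infusion entry is "Before the infusion: Cytokine analysis, including interleukin 1b (IL-1b), IL-6, Tumour Necrosis Factor (TNF-α) and IL-10". The next is "24 h after the infusion: Cytokine analysis, full blood examination (FBE), chimerism assessment and LFTs". The entries that cover one week are "4 day, 1 week and 1 month chimerism assessment" and "1 week, 1 month and 3 months post-transfusion: FBE and LFTs"; neither mentions cytokines.

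**Figure 1.** Blood for cytokines is taken at the intervention step, then "for cytokines (24 h) & assess for side effects (up to 48 h". The later blood draw is "for FBE, LFTs and chimerism (1w, 1m", again without cytokines.

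**Table 1.** The cytokine column is ticked at -2 to 0 h and at 24 h. The 7 d row is ticked for physical examination and for the combined FBE, chimerism and LFT column; its cytokine cell is blank.

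**Case report form.** No page has a named cytokine field at any time point. The nearest is a general laboratory column on the GVHD assessment page.

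**Statistical analysis.** Paired t-tests or Wilcoxon signed-rank tests compare laboratory parameters before and after infusion. The section does not say which post-infusion time point is used.

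**The concern.** An outcome definition says what will be reported; a schedule determines what is collected. Here they disagree, and the monitoring section points its readers to Figure 1 and Table 1. Staff who work from those, or from the laboratory list, would draw no cytokine sample at one week, and the case report form would not show them that one was missing. A serum sample that was not taken on day 7 cannot be taken later.

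At stake is the later of the two post-infusion readings for the immune-response objective. With 24 hours alone, the trial could describe an immediate change in cytokines but not whether it persists or has resolved by one week.

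**Working it through.** The check is a count of cytokine time points in each source.

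| Source | Before infusion | 24 h (1 day) | 7 d (1 week) |
| --- | --- | --- | --- |
| Protocol Synopsis | yes | yes | yes |
| Methods, Outcomes, Laboratory outcomes | yes | yes | yes |
| Laboratory list | yes | yes | no |
| Figure 1 | yes | yes | no |
| Table 1 | yes | yes | no |
| Case report form | no named field | no named field | no named field |

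**Step 1: rule out an extraction fault.** A blank cell in one table could be an artefact of reading the PDF. The laboratory list and Figure 1 are text, and both leave out day 7 in the same way, so the gap is in the plan.

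**Step 2: count the samples per infant.**
- Outcome definition: 1 before + 2 after = 3.
- Schedule: 1 before + 1 after = 2.
- Share of post-infusion time points missing: (2 − 1) / 2 = 50%.
- Share of all cytokine samples missing: (3 − 2) / 3 = one third.

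**Step 3: scale to the trial.** The Sample size section plans at least 20 infants, 10 per stratum, and says that fewer may be infused. For the four cytokines named (IL-1b, IL-6, TNF-α, IL-10), with complete sampling:
- 20 infants infused: 20 × 4 × 2 = 160 post-infusion values under the outcome definition, and 20 × 4 × 1 = 80 under the schedule.
- 10 infants infused (an assumption, to show the range): 10 × 4 × 2 = 80 against 10 × 4 × 1 = 40.

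These counts are illustrative, because the outcome text presents the four as part of a wider panel. The 50% and the one third depend on neither the number of infants nor the number of cytokines.

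**Step 4: effect on the analysis.** The paired comparison of baseline with 24 h keeps all its pairs. A paired comparison of baseline with day 7 would have none.

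**Step 5: pre-infusion liver tests.** Abnormal liver function tests are a listed sign of acute GVHD in the Monitoring section. The first LFT in the laboratory list, Figure 1 and Table 1 comes after infusion. The case report form has a field for the last serum chemistry on the day-of-infusion page, and an open pre-infusion laboratory cell on the GVHD page, where only chimerism is marked not applicable. No passage names LFTs before infusion. The form therefore leaves room for a baseline whose content the schedule does not define.

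**The case against.** **The loss is not certain.** Day 7 is stated in both the synopsis and the outcome definition, the trial recruits at one hospital, and blood is already drawn at one week from every infused infant. A team that knows the outcome text may well add the cytokine sample. This stands: a reader might infer that the day-7 samples will not be taken, but the documents support only that they may be missed if staff follow the schedule.

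**A fixed number of lost tests cannot be claimed.** Multiplying four cytokines by two time points suggests that four of eight planned comparisons would be empty. The Statistical analysis section names no time point and the cytokine list is open-ended, so the plan contains no such set of eight. The loss is properly stated as time points.

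**The outcome is secondary.** Cytokines enter neither the feasibility nor the safety criterion. That is right, and it limits how serious the point is.

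**Missing pre-infusion FBE and LFTs are not a contradiction.** A reader might infer that Table 1 drops tests ordered elsewhere, or that an infant with already abnormal liver tests could not be told apart from one with new liver involvement. Neither follows. No passage orders those tests before infusion, so Table 1 contradicts nothing. The case report form records the last serum chemistry and FBE and has an open pre-infusion laboratory cell, a physical examination precedes infusion, and the appendix on adverse events has baseline status recorded before cell therapy. What remains is narrower: serum chemistry may or may not include LFTs, and the documents do not say.

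None of these arguments removes the mismatch between the outcome definition and the three schedule sources.

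**Conclusion.** The plan is internally inconsistent on day-7 cytokines. The synopsis and the outcome definition require them; the laboratory list, Figure 1 and Table 1 leave them out; and the case report form gives no prompt. If the schedule is followed, one of two post-infusion time points is lost (50%, or one third of all cytokine samples) and the change from baseline to day 7 cannot be assessed. The 24 h comparison is untouched.

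This rests on one assumption, that staff sample by the schedule and not by the outcome text. It should be fixed, and preferably before further infusions, since a missed sample cannot be replaced. It does not threaten either primary outcome. The pre-infusion LFT question is a request for clarification only.

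**What to change.** Reconcile the passages so that the schedule delivers the outcome as defined:
- Table 1: tick cytokine analysis in the 7 d row.
- Laboratory list: add cytokine analysis at 1 week.
- Figure 1: add cytokines at 1 week, separately from the 1-month draw that shares the same line.

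The 1-week draw already exists, so no extra visit or venepuncture is needed. The cost is a document correction and some extra sample volume. The documents give no blood volumes, so the sponsor should confirm that the addition is acceptable in infants of this size.

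As a clarification, state whether the pre-infusion laboratory evaluation on the case report form includes LFTs, and make the schedule and the form agree.

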   1. ***Primary*:** To evaluate the safety and feasibility of administration of single-dose, at least 4/6 or higher HLA-matched allogeneic UCBC therapy in preterm infants with severe brain injury.
   2. ***Secondary:***
      1. To evaluate the effect of administration of allogeneic UCBCs on short and long-term clinical outcomes of enrolled preterm infants.
      2. To evaluate the effect of administration of allogeneic UCBCs on immune responses as measured by cytokine levels in enrolled preterm infants.
2. **METHODS**
   1. ***Design***

This is an open-label, phase-I, single-arm, feasibility, and safety study.

- 1. ***Setting***

The studies will be conducted at Monash Newborn, Monash Children’s Hospital, and Monash Medical Centre, Monash Health, in partnership with BMDI Cord Blood Bank, Parkville and Hudson Institute of Medical Research, Clayton.

- 1. ***Ethics***

The study will be conducted in compliance with the approved protocol/amendment(s), conditions of Monash Health Human Research Ethics Committee **(**HREC) approval, and the NHMRC National Statement on Ethical Conduct in Human Research 2007.^27^ A letter of study approval will be obtained from HREC prior to the commencement of the trial. Further, any amendments to the study will be submitted to HREC for approval prior to being implemented.

- 1. ***Participants***
     1. Inclusion criteria
        1. Preterm infants born before 28 completed weeks of gestation (up to 27+6 weeks, ALLO-1 trial) OR born between 28 and 36+6 weeks of gestation (ALLO-2 trial) AND
        2. Severe brain injury detected on neonatal neuroimaging any time after birth. Severe brain injury will be considered as grade 3 (IVH with ventricular distension) or 4 (parenchymal haemorrhagic infarct) IVH,^28^ and diffuse white matter injury like cystic (grade 3) PVL^29^ or significant white matter loss. If there is uncertainty regarding the severity of preterm brain injury, a discussion will be conducted with the clinical and radiological teams to assess and confirm whether the injury qualifies as severe.
     2. Exclusion criteria
        1. Infants with known major congenital anomalies OR
        2. Infants whose care is being redirected to comfort care.

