Cell therapy will only be administered when preterm infants are clinically stable, which is deemed by the treating physician. Also, infants should not be receiving antimicrobial therapy for confirmed or presumed late-onset neonatal sepsis, which is active at the time of cell infusion, as their course may be unpredictable and may confound adverse events falsely attributing to the cell therapy.

- 1. ***Recruitment and identification of potential participants***

Head ultrasound or magnetic resonance imaging (MRI) scans for preterm infants admitted to the neonatal intensive care unit at Monash Children’s Hospital will be reviewed by the study team daily to identify severe brain injury. If a severe brain injury is identified on the scan, the infant’s family will be approached for consent, provided all the additional criteria are met. The eligibility will be further re-confirmed before administering the intervention.

- 1. ***Consent***

The study team will explain verbally about the trial and will also provide the Participant Information and Consent Form to the parent or legal guardian. The participant's family will be given sufficient time for consideration and family discussion for providing written, voluntary consent that is free from coercion. The team member obtaining the informed consent will also sign the informed consent form. A copy of the consent form will be given to the parent or legal guardian. Documentation about the participant’s participation and voluntary consent will be noted in the electronic medical record. Participants’ families who wish not to participate in the trial will be recorded. Similarly, eligible participants who are not approached and participants who have a severe brain injury but are otherwise ineligible will be recorded in the enrollment log.

- 1. ***Sample size***

A minimum of 20 preterm infants, with 10 each in each stratum (<28 weeks, ALLO-1 trial and 28 to 36+6 weeks, ALLO-2 trial), will be enrolled to receive UCBCs at the dose range mentioned below, if appropriate HLA matching is achieved. This sample size is consistent with other cell therapy trials in newborn infants. The number of preterm infants recruited for the safety outcome (cell infusion) may be less as some eligible infants may not suffice the criteria required for HLA matching or may not survive to receive the infusion, but the aim is to assess feasibility for at least 10 infants in each stratum.

- 1. ***Intervention details***

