     1. HLA matching: Allogeneic UCBCs will be obtained from BMDI Cord Blood Bank with an HLA matching of at least 4/6. As HLA matching and processing UCBCs may be time-consuming, the eligibility (neuroimaging) will be reconfirmed before administering the allogeneic UCBCs after successful HLA matching.
     2. Age of administration: Allogeneic UCBCs will be administered via IV infusion anytime from birth until three months of life, generally within 2-3 weeks of diagnosis of confirmed severe preterm brain injury.
     3. Cell infusion: Only one allogeneic UCBC infusion will be administered intravenously.
     4. UCBC dose: The infusion is aimed for 50 million total nucleated cells (TNCs) per kilogram of body weight will be administered. This therapeutic dose is based on preclinical^30^ and clinical studies^5,6^ of UCBC for different types of perinatal brain injury.
     5. Route: The UCBCs will be administered intravenously via a peripheral intravenous cannula.
  2. ***Comparison***

There will be no control group as this is a single-arm, open-label, phase-I study.

- 1. ***Outcomes***
     1. Primary outcomes
        1. Feasibility: Allogeneic UCBC therapy will be considered feasible if there is an availability of at least 4/6 HLA-matched allogeneic UCBCs sourced from the BMDI Cord Blood Bank for >60% of eligible infants.
        2. Safety: Allogeneic UCBCs will be considered as safe if there are no serious adverse events related to UCBCs during and for 48 hrs post-infusion and the absence of GVHD in the first three months after cell infusion. The safety outcomes will be reported for eligible infants where feasibility is demonstrated, and allogeneic UCBCs are administered.
     2. Secondary outcomes
        1. Clinical outcomes: The following clinical outcomes will be reported for the infants who received infusion.
           1. Death, until 24 months of corrected age
           2. Moderate to severe bronchopulmonary dysplasia, assessed as oxygen or positive pressure requirement at 36 weeks of postmenstrual age
           3. Severe retinopathy of prematurity, assessed as any retinopathy requiring anti-VEGF or laser treatment before discharge
           4. Necrotising enterocolitis, assessed as bell stage 2 or more before discharge
           5. Culture-proven sepsis, bacterial or fungal, requiring antibiotics treatment for 7 or more days before discharge

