The criteria for eligibility will be confirmed on the day of infusion. The cell product will be obtained from the BMDI Cord Blood Bank a day before the transfusion. CBU released from the Cord Blood Bank for this study will have undergone all pre-release testing as routinely performed for release for bone marrow transplant, and have met compliance with the AusCord Quality & Release Criteria. The CBU will be released under “Exceptional Release” and the TGA notified as the bank is not licensed for the release of unrelated allogeneic non-homologous use. The product will be thawed at Monash Health Translation Precinct's Cell Therapy and Regenerative Medicine Platform. After thawing, washing of cells (to remove DMSO, a cryopreservant) will be undertaken using Dextran-Albumin and resuspended in 4% albumin as per standard clinical practice. Cell viability (>70% viable CD34+ cells, in accordance with the AusCord Quality & Release Criteria.) will be determined before administration. UCBCs will be administered intravenously (through a peripheral intravenous catheter) within one hour of thaw at a dose of 50 million (as available in aliquot) viable TNCs/ kg body weight. The exact dose will depend on the number of viable TNCs available in the final cell product. The volume of cell infusion(s) will be 10 mL/kg, and cell infusion will occur over one hour undertaken in the neonatal unit or the clinical trials facility of Monash Children's Hospital. The custody of care of the product will be transferred from BMDI Cord Blood Bank to the shipper to Monash Health Translation Precinct's Cell Therapy and Regenerative Medicine Platform to the clinical team using appropriate standard operating procedures.

- 1. ***Statistical analysis***

Descriptive statistics will be used to report demographics and outcomes. The categorical variables will be described as frequency and percentage and continuous variables as median (interquartile range) and mean (standard deviation), depending on the normality of the data, which will be determined by the Shapiro-Wilk test. The data will be analysed using STATA Version 17.0 (StataCorp LLC, College Station, TX, USA). Paired t-tests or Wilcoxon signed-rank tests will be performed to compare the laboratory parameters before and after infusion.

- 1. **Safety monitoring and reporting**
     1. Monitoring **(Figure 1 and Table 1):**
        1. The following will be monitored during and within 48 hours of infusion.
     - During infusion

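### The cytokine objective is worded as an effect of the cells, but the uncontrolled before/after test can only show change over time (minor; wording fix)

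*Combined protocol and SAP*

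**What the plan says.** All references are to the combined protocol and SAP.

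- **Trial objectives, Secondary:** "To evaluate the effect of administration of allogeneic UCBCs on immune responses as measured by cytokine levels in enrolled preterm infants". The Synopsis sets the same objective.
- **Synopsis, Secondary outcomes:** the laboratory outcome is itself named as an effect: "Laboratory outcomes: Effect of allogeneic UCBCs on infant’s cytokines levels". The matching entry under Methods, Outcomes is more neutral and says only that cytokines will be assessed.
- **Sampling times (Synopsis and Outcomes):** "just before UCBC administration and 1-day and 7-day post administration".
- **Comparison:** "There will be no control group as this is a single-arm, open-label, phase-I study".
- **Statistical analysis:** "Paired t-tests or Wilcoxon signed-rank tests will be performed to compare the laboratory parameters before and after infusion". Everything else in that section is descriptive.
- **Intervention details, age of administration:** "anytime from birth until three months of life, generally within 2-3 weeks of diagnosis of confirmed severe preterm brain injury".
- **Participants, after the exclusion criteria:** "Cell therapy will only be administered when preterm infants are clinically stable, which is deemed by the treating physician". Infants under treatment for active late-onset sepsis are also held back.

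**The concern.** The objective and the test have different null hypotheses. The objective's null is that the infusion does not alter cytokines. The paired test's null is that the mean or median within-infant difference between two dates is zero. The two coincide only if an uninfused infant's IL-1b, IL-6, TNF-α and IL-10 would stay level over the following 1 and 7 days. The plan neither states nor supports that assumption.

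The design gives reasons not to take it for granted. The baseline is one sample, generally taken in the weeks after a severe brain injury is diagnosed, so levels could still be settling. It is also taken at a moment chosen because the infant is stable, so levels could rise again later. Postnatal maturation, intercurrent illness and other treatment could act in either direction.

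What is at stake is what the trial may conclude. The Background describes an anti-inflammatory mechanism. A small p-value for an outcome named as a cell effect could be taken to confirm it when there is none, and an opposing natural change could hide a real one.

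**Working it through.** **1. Is there a figure of the plan's to reproduce?** No. The minimum of 20 infants (10 per stratum) rests on consistency with other newborn cell therapy trials. No alpha, power, effect size or SD is given for cytokines.

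**2. What the test estimates.** Let D be an infant's post-infusion value minus the pre-infusion value. In a single arm, mean(D) = natural change + cell effect. The paired test addresses the sum. With no uninfused infants and no series of samples before infusion, the planned data do not identify the two parts separately. This step needs no numerical assumption.

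**3. How much natural change would matter.** Inputs:
- n = 10 (one stratum) and n = 20 (both strata), from Sample size. That section warns that fewer may be infused.
- Two-sided alpha of 0.05: assumed, as the plan states none.
- Natural drift δ, in units of the SD of D: assumed, as the documents give neither size nor direction.
- Cell effect: set to zero.

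The paired t statistic then follows a noncentral t distribution with n − 1 degrees of freedom and noncentrality δ√n. The rejection probability is P(|T| > t(0.975, n−1)), with critical values 2.262 (n=10) and 2.093 (n=20).

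| Drift δ (SD of D) | n=10: δ√n | n=10: P(p<0.05) | n=20: δ√n | n=20: P(p<0.05) |
|---|---|---|---|---|
| 0 | 0 | 5.0% | 0 | 5.0% |
| 0.25 | 0.79 | 10.9% | 1.12 | 18.6% |
| 0.5 | 1.58 | 29.3% | 2.24 | 56.5% |
| 1.0 | 3.16 | 80.3% | 4.47 | 98.9% |

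Simulated Wilcoxon signed-rank tests on normal changes give similar rates (at δ = 0.5: 29% for n=10, 54% for n=20). More infants make the spurious signal more likely, because the test is detecting a real change; only its cause is in doubt.

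**4. Masking.** With a true fall of 0.9 SD and a natural rise of 0.45 SD, the net shift is 0.9 − 0.45 = 0.45 SD. Power falls from 72% to 25% at n=10 and from 97% to 48% at n=20.

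**5. Day 1 and day 7 differ.** As an illustration, assume a steady drift of 0.06 log units per day and a within-infant SD of 0.5, so that SD(D) = 0.5 × √2 = 0.707.
- Day 1: δ = 0.06/0.707 = 0.085. Rejection is 5.7% (n=10) and 6.5% (n=20), close to nominal.
- Day 7: δ = 7 × 0.06/0.707 = 0.594. Rejection is 39% (n=10) and 71% (n=20).

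A slow drift therefore matters mainly at day 7. A fast rebound could matter at day 1, but nothing in the documents quantifies one.

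**6. Is the day-7 sample scheduled?** The Synopsis and the Outcomes section promise cytokines at day 7. The laboratory list under Safety monitoring, the text of Figure 1 and Table 1 show cytokines only before infusion and at 24 h; the 7-day row of Table 1 has no cytokine mark. As scheduled, the comparison most exposed to slow drift has no sample.

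**The case against.** The strongest reply is that the design is openly single-arm and phase I, that cytokines are secondary, and that the analysis sentence claims only to compare values before and after infusion. All of that stands. Nothing here calls for a control arm, and the test is valid for the question it actually answers. What remains is that the objective and the Synopsis outcome use the word effect, and no sentence tells the reader not to carry that word over to the p-value.

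A second reply is that the drift is entirely assumed. That also stands. Without drift the test keeps its 5% level per comparison, and the table above shows how a t-test behaves at chosen shifts; it says nothing about these infants.

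A reader might go further and infer that the plan will report natural drift as a cell effect, or that a false signal is likely. The documents support neither. They do not say how a significant change will be described, and they contain no cytokine time course.

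A reader might also think that existing data could correct for drift, for instance by modelling cytokines on days since diagnosis. The documents do not support this either. With one pre-infusion sample per infant, the slope would lean on comparing infants infused early with those infused late, and those groups may differ because infusion waits for stability. A rebound starting at infusion could not be told apart from the post-infusion terms. The case report form has no dedicated field for date of injury diagnosis, and the day-7 sample is missing from the schedule.

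**Conclusion.** The point holds as a mismatch between the wording of the objective and what the test can answer. It follows from the text alone: an effect objective, no control group, one pre-infusion sample, a test of zero change, and no limit on interpretation.

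Its numerical consequence is conditional. Under a two-sided 5% test, normally distributed changes and no cell effect, assumed drifts of 0.25 to 1.0 SD give p<0.05 in about 11% to 80% of trials at n=10 and 19% to 99% at n=20. Under a slow steady drift the excess is small at day 1. The actual drift is unknown in size and direction.

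The point is minor. It concerns a secondary outcome and leaves the primary feasibility and safety conclusions untouched.

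**What to change.** 1. In the Synopsis and under Trial objectives, restate the laboratory objective and outcome as *change in cytokine levels from before infusion to 1 and 7 days after*. Align the laboratory entry under Outcomes.
2. Under Statistical analysis, state that the paired tests assess change over time, that results will be given as mean or median change with a 95% CI, and that they will not be interpreted as an effect of the cells. For a mean change, the CI half-width is t(0.975, n−1)/√n: 2.262/√10 = 0.72 SD at n=10 and 2.093/√20 = 0.47 SD at n=20.
3. Reconcile the day-7 cytokine sample in the Synopsis and Outcomes with the laboratory list under Safety monitoring, Figure 1 and Table 1, which schedule cytokines only before infusion and at 24 h.
4. Do not add a drift-adjusted model. For the reasons given under the objection, an adjusted estimate could make a causal reading look better supported than it is.

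The cost is a few sentences of protocol text and a weaker stated claim for a secondary outcome. The rewording needs no extra infants or samples. Whether the day-7 sample is additional to what is now scheduled depends on how item 3 is resolved.
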